#### 6.1.3 Handling of dropouts and missing data

Subjects dropping out from the trial before surgery will be replaced. Subjects dropping out after surgery during the recruitment period will be compensated for using continuous recruitment. Subjects dropping out after surgery and after the completion of the recruitment period will be compensated for in the sample size estimation, see section 6.5.

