### **Screening and inclusion**

- After obtaining the subject's written informed consent and verifying that the subject fulfils all inclusion and none of the exclusion criteria the subject will be included in the study and given a Subject Id.
- A reference venous blood sample/s will be taken from each subject before surgery, for analyses of Hb, haematocrit/erythrocyte particle count (Hct/EVF), sodium ( $\text{Na}^+$ ), potassium ( $\text{K}^+$ ), thrombocyte particle count (TPC), C-reactive protein (CRP), leukocyte particle count (LPC), creatinine and Glomerular Filtration Rate (GFR)/Creatinine Clearance ( $\text{C}_{\text{Cr}}$ ). Haemoglobin (Hb) concentration  $> 9.0 \text{ g/dl}$  ( $5.6 \text{ mmol/l}$ ) and normal creatinine/clearance levels will be verified.
- Subject ID will be allocated based on clinic number and procedure (primary or secondary surgery and treatment group given from randomization).
- Demographics will be collected and registered in the Case Report Form (CRF).
- Medical and surgical history as well as medications will be registered in the CRF.

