**Table 1 Study plan**

|                                              | Screening              | Pre-op                     | Post-op follow up                                                                 |                                      |                                      |                                      |                                      |                     |                            |
|----------------------------------------------|------------------------|----------------------------|-----------------------------------------------------------------------------------|--------------------------------------|--------------------------------------|--------------------------------------|--------------------------------------|---------------------|----------------------------|
| Visit no/sampling time                       | 1                      | 2                          | 3                                                                                 | 4                                    | 5                                    | 6                                    | 7                                    | 8                   | 9                          |
| Visit Description                            | Screening              | Pre-op                     | 3 h                                                                               | Day 1                                | Day 2                                | Day 3                                | Day 4                                | Discharge           | Month 2                    |
| Visit Window
(Hours/days $\pm$ No. Hours) | Before or at admission | Before general anaesthesia | 3h ( $\pm$ 1h), after end of surgery and before post-op transfusion if applicable | 24h ( $\pm$ 6h) after end of surgery | 48h ( $\pm$ 6h) after end of surgery | 72h ( $\pm$ 6h) after end of surgery | 96h ( $\pm$ 6h) after end of surgery | At day of discharge | 8w (5-12w) after discharge |
| Informed consent                             | X                      |                            |                                                                                   |                                      |                                      |                                      |                                      |                     |                            |

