### 3.5 Method of assigning subjects to treatment groups

Each participating clinic will be given a range of Subject ID for use for their included patients. The distribution between clinics will be as follows:

| Clinic No. | Subject ID range | Subject ID range for primary procedures | Subject ID range for secondary procedures |
|------------|------------------|-----------------------------------------|-------------------------------------------|
| Clinic 1   | 1101-1299        | 1101-1199                               | 1201-1299                                 |
| Clinic 2   | 2101-2299        | 2101-2199                               | 2201-2299                                 |
| Clinic 3   | 3101-3299        | 3101-3199                               | 3201-3299                                 |
| Clinic 4   | 4101-4299        | 4101-4199                               | 4201-4299                                 |
| Clinic 5   | 5101-5299        | 5101-5199                               | 5201-5299                                 |
| Clinic 6   | 6101-6299        | 6101-6199                               | 6201-6299                                 |

Subjects will be allocated their Subject ID in a strictly consecutive/sequential order when eligibility for inclusion has been established. Each Subject ID has a corresponding randomization code referring to the appropriate treatment allocation. The randomization process will be performed in a blinded approach, either with a web-based login system or by randomization envelopes that cannot be seen through without opening. If a subject discontinues from the study, the subject number will not be reused, and the subject will not be allowed to re-enter the study. However, during the recruitment period a drop-out subject may be replaced by a new included patient with the Subject ID next in turn in addition to the planned total number of subjects for the specific clinic (see section 6.1.3).

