### 3.6 Blinding and procedures for unblinding the study

#### 3.6.1 Methods for ensuring blinding

It is not possible to double blind this study due to the fact that it will be obvious for the study site team to which group the patient has been allocated. I.e. patients in the test group will have their blood collected with the Sangvia® device and in the control group no autologous blood salvage will be performed. The decision of blood bank transfusion will however be assessed in a blinded fashion with an independent assessors unaware of the patient treatment allocation. I.e. each decision of bank blood transfusion will be taken based on transfusion triggers by an assessor unaware of the treatment group whenever possible and the reason/s for the transfusion will be registered. For cases when the decision of bank blood transfusion are taken by a responsible investigator aware of the treatment allocation, e.g. in an emergency situation during surgery, the registered reasons for transfusion will be reviewed by an independent assessor/committee who are unaware of the treatment allocation. Inconsistency in transfusion decision between the independent assessor/committee and the responsible investigator will be reflected in the per protocol analysis where patients with suspected biased transfusion decisions will be excluded. Laboratory sample analyses will be done by assessors unaware of the patient treatment allocation.

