## 6.5 Determination of sample size

The primary variable and objective is the base for the sample size calculation. The sample size formula used is referred to in Lachin 1981.

$$N = \frac{(Z_{\alpha} + Z_{\beta})^2 4\bar{\pi}(1 - \bar{\pi})}{(\pi_s - \pi_c)^2}$$

Where:

N = total number of patients

$Z_{\alpha} = 1.96$  ( $\alpha = 0.05$ )

$Z_{\beta} = 1.2816$  ( $1 - \beta = 0.90$ )

$$\bar{\pi} = \frac{\pi_s + \pi_c}{2}$$

An estimation normal use of allogeneic blood of 21% is based on reported values in the literature. It is acknowledged that in revision surgery a higher percentage of allogeneic blood transfusions is seen than in primary total hip replacements. Because revision patients requiring serious bone grafting are excluded, the percentage of revision patients is expected to be just slightly higher than for the average primary total hip. A high number of revision, e.g. a maximum of 30%, in the total group of patients is considered to have limited effect of the total transfusion rate but are accounted for in the 21% assumed for the total group. The expected values of transfusion rate in the Sangvia® group is estimated to lie around 7%. Accordingly, imputing the values for the estimated transfusion rates in the test and control group generates a mean transfusion rate value of 14%. The sample size necessary for detection of this expected difference in transfusion rate frequency is calculated to 260 patients (5% significance level, two-sided hypothesis, 90% power). Additional 40 patients will be included in the study to compensate for drop-out. In summary, 300 patients will be included in total and 150 in each treatment group.

The transfusion rate of bank blood is considered to vary dependent on type and complexity of surgery. Greatest normal use and differences between the groups are expected in the subgroup with medium (surgery duration 1-2 hours) to complex (surgery duration more than 2 hours) surgery complexity why power are considered to be adequate for the planned subgroup analyses in these groups.

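### The arm can be open to the site before surgery, and subjects who leave in that interval are replaced even if already randomised, so selective loss after randomisation is possible

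*Protocol*

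**What the plan says.** **Assignment.** Section 3.5 issues Subject IDs consecutively once eligibility is established, through a web login or opaque envelopes, and adds: "Each Subject ID has a corresponding randomization code referring to the appropriate treatment allocation". The Screening and inclusion list in 3.1 also places the ID in that step, but describes it differently: "Subject ID will be allocated based on clinic number and procedure (primary or secondary surgery and treatment group given from randomization". Table 1 times screening as "Before or at admission". Setting up the device comes later, in the preoperative step.

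**Openness.** Section 3.6.1 gives as the reason that double blinding is impossible that "it will be obvious for the study site team to which group the patient has been allocated".

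**Leaving.** Section 3.3.5.1 allows discontinuation at any time. The reasons include the subject's own choice, safety, severe non-compliance and incorrect enrolment. Safety and non-compliance are judged by the investigator and/or the sponsor.

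**Replacement.** Section 6.1.3: "Subjects dropping out from the trial before surgery will be replaced". Section 3.5 gives the mechanism: "a drop-out subject may be replaced by a new included patient with the Subject ID next in turn". Numbers are not reused and the subject cannot re-enter.

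**Analysis sets.** Section 6.3 bases efficacy conclusions on the Per Protocol (PP) set, which requires treatment according to the protocol. The other set is named All Patient Treated (APT) but is defined as containing all patients.

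**The concern.** Randomisation protects the comparison only while the randomised groups stay intact. Here the arm may be known some time before surgery, and in that interval people who know it may decide whether the subject stays. If those who leave one arm differ in transfusion risk from those who leave the other, the operated groups differ before the device has been used. Recruiting another subject makes up the number but does not bring back the one who was lost.

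This bears directly on the primary variable. Section 3.2 already accepts that the comparison may be biased because the trial can hardly be blinded. Its safeguards there cover the transfusion decision, not retention between assignment and surgery. Stratification by clinic and by type of surgery does not help, since selection can occur within a stratum. An analysis plan could define a further set, but it could not change when the code is released or which subjects are replaced during recruitment.

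**Working it through.** **1. The plan's own figure.** Inputs from 6.5: "5% significance level, two-sided hypothesis, 90% power"; "An estimation normal use of allogeneic blood of 21% is based on reported values in the literature"; 7% in the Sangvia group; mean rate 14%.

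N = (1.96 + 1.2816)² × 4 × 0.14 × 0.86 / (0.07 − 0.21)² = 10.508 × 0.4816 / 0.0196 = 258.2

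Rounded up to equal arms this is 260, as stated. Adding 40 gives 300, or 150 per arm. The sample size is not in dispute.

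**2. Is an open interval permitted?**

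- The ID fixes the arm (3.5), and the ID is issued at screening and inclusion (3.1).
- Screening may precede admission (Table 1).
- No sentence holds the code until surgery.

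An interval is therefore permitted, but its length is not stated.

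**3. Which comes first, ID or arm?** In 3.5 the consecutive ID determines the arm. Read literally, the 3.1 list bases the ID partly on the arm. The two must be reconciled, because sequential allocation protects the sequence only if the ID comes first.

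**4. What happens to a randomised subject who leaves before surgery?**

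- 6.1.3 and 3.5: replaced by the next ID, with no distinction by randomisation status.
- PP set: not treated according to the protocol, so not included.
- APT set: excluded by its name, included by its definition, so unclear.

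**5. How much could it matter?** The documents give neither the number of such leavers nor their risk, so this is an illustration only. Assumptions:

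- a fraction f of one arm leaves before surgery;
- leavers would have had a 48% transfusion risk (no source in the protocol);
- replacements are ordinary patients at 21%;
- 150 are analysed per arm, although a replacement by next ID need not enter the arm that lost the subject;
- two-sided Fisher exact test, rejecting at p ≤ 0.05, computed by full enumeration.

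Rate among those who remain: (0.21 − 0.48f)/(1 − f). After ordinary replacements the arm's rate is

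(1 − f) × (0.21 − 0.48f)/(1 − f) + 0.21f = 0.21 − 0.27f

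| f | Rate in the affected arm | Type I error: no device effect, loss in test arm | Power: 7% v 21%, loss in control arm |
|---|---|---|---|
| 0 | 21.00% | 3.6% | 93% |
| 2% | 20.46% | 3.7% | 91% |
| 5% | 19.65% | 4.4% | 88% |
| 10% | 18.30% | 6.8% | 81% |

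If leavers have the same 21% risk as everyone else, the rate stays at 21% for any f and there is no bias.

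**The case against.** A reader might infer more than the documents support.

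- **That the arm is assigned before the eligibility bloods are verified.** This would rest only on the order of the bullets in the 3.1 list. The first bullet gives the ID after all criteria are verified, renal function and Hb are themselves exclusion criteria, and 3.5 says the same. The bullet that allocates the ID also follows the blood check.
- **That concealment is lost.** Consecutive IDs, a web login or opaque envelopes, no reuse of numbers and no re-entry conceal the arm up to assignment. A replacement takes the next ID, so a site cannot choose its arm. What remains is selective loss after randomisation, which is a different problem.
- **That leavers vanish.** IDs are not reused, and 3.3.5.2 has reasons and adverse events asked for at discontinuation. What the protocol lacks is a clear rule on reporting and counting these subjects by arm.
- **That the 40 extra patients (40/300) show how large the loss may be.** Section 6.1.3 ties that allowance to drop-out after surgery and after recruitment has ended, so it says nothing about loss before surgery.

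Two further objections have force. The 3.6.1 sentence goes on to explain itself by use of the device, so it shows that the arm is open but not when it becomes known. And replacement is not itself the source of bias: if nobody were replaced, the rate among those who remain would still be shifted. The replacement rule matters because it treats a randomised leaver as someone whose place has been filled.

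These points narrow the concern. They do not close the interval or settle how these subjects are counted.

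**Conclusion.** The point holds in limited form. The protocol permits an interval before surgery in which the arm is open and a subject may leave or be discontinued on judgement. It replaces such subjects whether or not they were randomised, and it bases efficacy on a set that omits them. Arm-related loss could bias the transfusion comparison in either direction.

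The size is unknown. Under the assumed 48% risk, a one-arm loss of 2% is negligible. A loss of 5% raises type I error relative to its 3.6% starting point but leaves it below the nominal 5%. At 10% it passes the nominal level (6.8%). The effect on power is larger: 12 points at a 10% loss from the control arm. All of this requires that leaving is related both to the arm and to transfusion risk; nothing in the protocol shows that it will be. The change is worth making because it is cheap, not because serious bias has been demonstrated.

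**What to change.** 1. In 3.1 and 3.5, state that the Subject ID and randomisation code are released only after the screening laboratory results are verified, as close to surgery as feasible and before the device is set up. Use a screening number until then. This step does most of the work, because it shortens the interval.
2. Reconcile the 3.1 list with 3.5 so that the consecutive ID determines the arm.
3. In 3.5 and 6.1.3, replace only subjects who leave before randomisation. Recruitment beyond the planned number may continue after that, but it does not remove the earlier subject.
4. Report every randomised subject by arm, with the reason for leaving. Compare the transfusion rate in all randomised subjects who have surgery, as assigned, alongside the PP analysis. That comparison still omits subjects who leave before surgery, so the report by arm is needed to show whether losses were balanced.

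The cost is protocol wording, plus keeping a device set on hand for each study case because the arm is learned late. No extra patients or visits are needed.

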#### 6.1.4 Multi-centre

This study is a multi-centre study and there is no a priori reason to suspect that there will be any qualitative differences between the centres. However, local treatment routines at different clinics

are considered to potentially affect the outcome of the primary variable why stratification for each clinic will be made. This is considered to ensure equal distribution between test and control group patients why primary statistical analysis will not include centre in the model. The result of the primary variable will however be presented by centre as part in subgroup analyses.

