##### 4.3.3.2 Derivation or calculation of variable

The days between surgery and discharge will be calculated and the total time and time per type of care facility will be compared between treatment groups for every clinic.

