#### 6.1.2 Covariates and prognostic variables

Bleeding volume or complexity of surgery, i.e. surgery time, are considered to possibly influence outcome of the primary variable why stratification for either primary or secondary/revision hip surgery will be made at each recruiting clinic to ensure equal distribution in the two groups. Subgroup analyses of type (primary and secondary) and complexity (easy < 1 hour, medium 1-2 hours and complex > 2 hours) of surgery are planned to further investigate the correlation between the primary outcome and these factors.

Age is also an potential factor that may have an impact on the outcome of the primary variable. It is however considered that randomization as such will ensure approximately equal age distribution in the two treatment groups. Differences in age between the treatment groups will be evaluated and tested using Wilcoxon rank sum test in the analysis.

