## 6.2 Description of outcome variables in relation to objectives and hypotheses

The primary variable, transfusion rate, will be measured as the proportion ( $\pi$ ) of patients in each treatment group that is receiving allogeneic blood transfusion of the total number of patients in each treatment group. The hypothesis to be tested is:

$$H_0 = \pi_s = \pi_c$$

versus

$$H_1 = \pi_s \neq \pi_c$$

Where:

$\pi_s$  = Proportion patients treated with Sangvia® that require allogeneic blood transfusion in addition to Sangvia® transfusion.

$\pi_c$  = Proportion patients in the control group that require allogeneic blood transfusion.

The hypothesis will be tested using the Fischer Exact Test. The hypothesis will be rejected if the p-value is  $\leq 0.05$ .

Secondary objectives will be tested using similar hypotheses. The total and variable specific proportion values for infection rate, use of post-operative antibiotics and adverse events will be tested between the groups using the Fischer Exact Test. Continuous variables (e.g. post-op Hb values) will be compared and tested using the Wilcoxon Rank Sum test. Laboratory blood markers will also be evaluated for changes over time within each treatment group and this change will be tested using the Wilcoxon Signed Rank test.

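### Randomisation is stratified by clinic and surgery type, but the primary test is a plain Fisher test that expressly omits centre; a stratified test would recover about 3 to 5 points of power, mostly lost to Fisher's discreteness

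*Protocol*

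**What the plan says.** Section 6.1.2 names surgical complexity as a possible influence on the primary outcome, so "stratification for either primary or secondary/revision hip surgery will be made at each recruiting clinic". Section 3.5 carries this out with separate Subject ID ranges for primary and secondary procedures at each of six clinics, which makes 6 × 2 = 12 strata. Section 6.1.4 says that local routines "are considered to potentially affect the outcome of the primary variable why stratification for each clinic will be made". It then argues that this secures balance between the arms, "why primary statistical analysis will not include centre in the model". Centre results appear only among the subgroup presentations.

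For the primary comparison of overall transfusion proportions, section 6.2 states: "The hypothesis will be tested using the Fischer Exact Test". Surgery type does not enter that test either. Section 6.5 sizes the trial at 260 evaluable patients plus 40 for drop-out ("5% significance level, two-sided hypothesis, 90% power"), using a normal-approximation formula.

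For length of stay, section 4.3.3.2 says that times "will be compared between treatment groups for every clinic". Sections 6.2 and 6.4 apply a Wilcoxon rank sum test to continuous variables between the two groups.

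**The concern.** The protocol identifies two factors as potentially prognostic, builds both into the randomisation, and then gives the resulting balance as its reason for leaving one of them out of the test. The other is left out without comment. When allocation is balanced within prognostic strata, the arms differ by chance less than an unstratified test assumes. The variance is then overstated and the test runs below its nominal level. Fisher's test on a two-by-two table is already conservative because the table is discrete.

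The stake is efficiency on the primary endpoint: power that the stratified design could deliver is not collected, and the 90% in section 6.5 was not calculated for the test named in section 6.2. The balance argument is also least secure where it matters most. Section 6.3 bases efficacy conclusions on the per-protocol set, which drops patients after randomisation, so balance by stratum is not guaranteed there.

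**Working it through.** **Inputs from the protocol.** Control rate 21%, test rate 7%, mean 14%, two-sided 5%, 260 evaluable (130 per arm), 300 enrolled (150 per arm), all from section 6.5; six clinics and two surgery types from section 3.5.

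**Assumptions.** The protocol gives no clinic-specific rates. Three spreads of clinic control rates were used, each averaging 21%: none; moderate (about 8% to 39%); strong (about 2% to 55%). Arms are balanced within strata. CMH is without continuity correction.

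**Step 1: the plan's own figure.** N = (Zα + Zβ)² × 4 × π̄(1 − π̄) / (πs − πc)² = (1.96 + 1.2816)² × 4 × 0.14 × 0.86 / 0.14² = 258.2. The stated 260 is reproduced.

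**Step 2: the planned test with no clinic differences.** Exact enumeration at 130 per arm gives Fisher a size of 3.3% at a common rate of 14% and 3.6% at 21%, with power of 88.8%. Fisher reaches 90% at about 135 per arm (270 in total).

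**Step 3: separating the two causes.** Comparing Fisher with CMH changes two things at once, so an unstratified chi-square test is placed between them. Each scenario used 200,000 simulated trials, 130 per arm, with six clinic strata.

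| Clinic spread (assumed) | Fisher size | Chi-square size | CMH size | Fisher power | Chi-square power | CMH power |
|---|---|---|---|---|---|---|
| None | 3.3–3.6% | 4.9–5.0% | 4.9–5.0% | 88.8% | 91.7% | 91.7% |
| Moderate | 2.8–3.0% | 4.2% | 4.9–5.0% | 89.4% | 92.2% | 93.0% |
| Strong | 1.7–2.0% | 2.7–3.3% | 4.9–5.0% | 90.6% | 93.3% | 95.3% |

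- Power lost to Fisher's discreteness (chi-square minus Fisher): 2.9, 2.8 and 2.7 points.
- Power lost by omitting centre (CMH minus chi-square): 0, 0.8 and 2.0 points.
- Total (CMH minus Fisher): 2.9, 3.6 and 4.7 points.

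**Step 4: surgery type.** Section 6.5 expects revision rates only slightly above primary. With an assumed odds ratio of 1.3 and 12 strata, CMH power is 91.8%, 93.0% and 95.3%, which is practically unchanged.

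**Step 5: all 300 evaluable.** At 150 per arm Fisher's power is 93.2%, 93.7% and 94.6%.

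**Step 6: dependence on balance within strata.** If allocation were not balanced within strata, size at a 14% rate would stay at about 3.3% (Fisher) and 4.9% (chi-square) under both the moderate and the strong spread. Section 3.5 describes sequential codes by clinic and procedure but no block size, so the balance is intended rather than documented.

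**Step 7: type of CMH test.** With a continuity correction, CMH has size of 3.1–3.4% and power of 88.5%, 90.0% and 92.9%, so most of the gain disappears.

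**The case against.** The strongest defence is that nothing invalid is planned. Section 6.1.4 argues that balance by clinic stops local routines from confounding the comparison, and on bias that is correct. Fisher's test keeps type I error at or below 5% and is a common, defensible choice. The trial enrols 300, where Fisher's power exceeds 93%; at 260 with no clinic differences the shortfall against 90% is about one point. All of this stands, and it makes the point one of efficiency rather than validity.

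Three stronger readings are tempting, and the protocol does not support them.

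- A reader might infer that leaving centre out is what takes the test well below 5% and costs the whole 3 to 5 points. With little clinic variation nearly all of that comes from Fisher. Omitting centre matters appreciably only under wide clinic differences that the protocol does not quantify. Clinic-by-clinic use of tranexamic acid (section 3.3.4) makes differences plausible but gives no size.
- A reader might call the reasoning in section 6.1.4 backwards. It is incomplete: it addresses confounding and is silent on variance.
- A reader might take section 4.3.3.2 to mean that length of stay gets only six small clinic tests. Sections 6.2 and 6.4 supply an overall Wilcoxon rank sum test, so the defect is an unreconciled wording.

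**Conclusion.** The mismatch between a stratified design and an unstratified primary test is in the protocol's own text, and an analysis plan could not correct it without contradicting section 6.1.4. At 260 evaluable patients the planned test has an actual size of about 3.3% and power of 88.8% with no clinic differences, against about 5% and 91.7% for CMH. About 3 points of that gap are due to Fisher's discreteness whatever the clinic spread. Omitting centre adds 0 to 2 points over the assumed range from no spread to about 2% to 55%, and only if allocation is balanced within strata. Surgery type contributes little on the protocol's own expectation. No inflation of type I error arises. The practical effect is modest, but the improvement is nearly free.

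**What to change.** 1. In section 6.1.4, delete the statement that centre is left out of the primary analysis.
2. In sections 6.2 and 6.4, make the primary test a two-sided CMH test without continuity correction, stratified by clinic and type of surgery. Report the Mantel-Haenszel risk difference with its 95% confidence interval. Keep Fisher's exact test as a sensitivity analysis.
3. Specify in advance how sparse strata are pooled, for example by merging surgery types within a clinic. Section 6.5 mentions up to 30% revisions and the minimum per clinic is 20 patients; if that share applied there, the revision stratum would hold 20 × 0.30 = 6 patients and, at a 14% mean rate, 6 × 0.14 = 0.84 expected events. Strata without events contribute nothing to the test.
4. In section 6.5, base the power statement on the test that will be used. If Fisher is kept as primary, about 270 evaluable patients are needed for 90% under the stated rates.
5. Reconcile section 4.3.3.2 with sections 6.2 and 6.4, preferably as one van Elteren (stratified Wilcoxon) test for length of stay over the same strata, with per-clinic results descriptive.

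The cost is analysis wording only, with no extra patients or data. The change should be made before any comparative data are seen, and so before the interim look in section 6.6.

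### Balance from stratified randomisation is given as the reason to leave centre out of the primary test; it is a reason to stratify that test, for a modest gain in power

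*Protocol*

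**What the plan says.** Randomisation uses two factors. Protocol 6.1.2 states that "stratification for either primary or secondary/revision hip surgery will be made at each recruiting clinic", because bleeding and surgical complexity may influence the primary variable. Section 6.1.4 adds that local routines at the clinics may affect it as well. Section 3.5 carries both factors into the Subject ID ranges: six clinics, each with a primary and a secondary series, so 12 strata.

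Section 6.1.4 then argues that this stratification makes the arms comparable, "why primary statistical analysis will not include centre in the model". Section 6.2 fixes the test: "The hypothesis will be tested using the Fischer Exact Test", comparing two overall proportions and rejecting at p ≤ 0.05. Centre and surgery type return only as subgroup presentations (6.1.4, 6.3).

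Only the omission of centre is stated and argued. Surgery type drops out because the test in 6.2 is pooled.

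**The concern.** If stratum k has transfusion rate p_k and weight w_k, with overall rate p̄, then

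p̄(1 − p̄) = Σ w_k p_k(1 − p_k) + Σ w_k (p_k − p̄)².

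A pooled test uses the whole left-hand side as its error variance. When the arms are balanced within strata, the between-stratum term (the last one) no longer contributes to chance differences between the arms. The pooled test still charges for it, so it becomes conservative to the extent that the strata are prognostic. Balance is therefore the condition under which a stratified analysis pays, not one that makes it unnecessary.

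Clinic differences are plausible. Tranexamic acid is allowed if it is used for all patients at a clinic (3.3.4, 3.7), so its use can differ wholly between clinics. Above the haemoglobin trigger, transfusion rests on the investigator's judgement (3.1). At stake is efficiency: section 6.6 itself foresees rates that would leave the study inconclusive and lead to additional patients.

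**Working it through.** **Inputs from the protocol (6.5).** Control rate 21%, Sangvia rate 7%, mean 14%, two-sided 5%, 90% power, 260 patients plus 40 for drop-out: "300 patients will be included in total and 150 in each treatment group". Revision share up to 30%. Six clinics × two surgery types = 12 strata.

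**Assumed, not in the documents.** The spread between clinics, the size of the surgery-type effect, equal clinic sizes, a common odds ratio, perfect 1:1 balance within strata, and a smaller effect of 21% v 10%.

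**Step 1: the plan's own figure.** N = (1.96 + 1.2816)² × 4 × 0.14 × 0.86 / 0.14² = 10.508 × 0.4816 / 0.0196 = 258.2, against 260 stated. It reproduces. The formula is a normal approximation without continuity correction.

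**Step 2: Fisher's share, with no strata effect (exact enumeration).**

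| Quantity | Per arm | Fisher | Pooled chi-square |
|---|---|---|---|
| Size, both 14% | 130 | 3.3% | 4.9% |
| Size, both 14% | 150 | 3.4% | 4.9% |
| Size, both 21% | 130 | 3.6% | 5.0% |
| Size, both 21% | 150 | 3.6% | 5.0% |
| Power, 21% v 7% | 130 | 88.8% | 91.7% |
| Power, 21% v 7% | 150 | 93.1% | 95.0% |

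Fisher alone costs 91.7 − 88.8 = 2.9 points at 260 patients and 95.0 − 93.1 = 1.9 (1.8 unrounded) at 300. At 21% v 10% with 150 per arm and no clinic effect, simulated power is 70.7% for Fisher and 75.7% for chi-square, a cost of 5.0 points.

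**Step 3: the strata share at 21% v 7%.** Simulation, 200,000 trials per scenario, 30% revision. With n_k patients per arm in stratum k, a_k events in the test arm and m_k in both, the CMH statistic is [Σ(a_k − m_k/2)]² / Σ[m_k(2n_k − m_k) / (4(2n_k − 1))], rejecting above 1.96². Chi-square to CMH isolates the strata share. Cells show Fisher / chi-square / CMH in %; size is at a common 14%.

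| Assumed spread (control stratum rates) | Size, 260 | Power, 260 | Power, 300 |
|---|---|---|---|
| None (21%) | 3.3 / 4.9 / 5.0 | 88.8 / 91.6 / 91.7 | 93.1 / 94.9 / 95.0 |
| Mild (13–35%) | 3.2 / 4.7 / 5.0 | 89.0 / 91.8 / 92.2 | 93.3 / 95.1 / 95.3 |
| Moderate (7–48%) | 2.7 / 4.2 / 4.9 | 89.4 / 92.3 / 93.2 | 93.7 / 95.4 / 96.0 |
| Strong (3–64%) | 2.2 / 3.4 / 4.9 | 90.4 / 93.1 / 94.8 | 94.4 / 96.1 / 97.1 |
| Extreme (1–76%) | 1.5 / 2.4 / 4.9 | 91.7 / 94.2 / 96.7 | 95.5 / 96.9 / 98.4 |

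The rates shown are for the 260-patient power runs. Unrounded, the strata share of power is 0.3 (mild), 0.9 (moderate), 1.7 (strong) and 2.6 (extreme) points at 260, and 0.2, 0.5, 1.0 and 1.5 at 300.

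**Step 4: the same split at 150 per arm with normally spread clinics** (surgery-type odds ratio 1.2, 40,000 trials).

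| Effect | Clinic SD (log odds) | Fisher | Chi-square | CMH | Fisher's share | Strata share |
|---|---|---|---|---|---|---|
| 21% v 7% | 1 | 93.9 | 95.7 | 96.6 | 1.8 | 0.9 |
| 21% v 10% | 0.5 | 71.3 | 76.5 | 77.5 | 5.2 | 1.0 |
| 21% v 10% | 1 | 72.1 | 77.6 | 80.9 | 5.5 | 3.3 |

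At 21% v 7% with SD 0.5, chi-square has 95.3% and CMH 95.6%, a share of 0.3. A further run put the largest strata share at 21% v 10% at about 3.5 points. With clinic rates of about 4–47%, size is 2.4% (Fisher), 3.5% (chi-square) and 5.0% (CMH).

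**Step 5: continuity correction.** At 260 patients a continuity-corrected CMH test has size 3.0–3.4%. Its power at 21% v 7% with no clinic effect is 88.5%, no better than Fisher's 88.8%.

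**The case against.** Much of the case on the other side stands.

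- A reader might infer that ignoring the strata is what makes the test run well below 5%. It is not the main cause unless clinic differences are strong. Size is already 3.3–3.6% with no strata effect, and even with a clinic SD of 1 Fisher's exactness takes the larger part of the power loss (5.5 of 8.8 points at 21% v 10%).
- A reader might infer that the trial is underpowered or its p-value invalid. At the protocol's own alternative the planned test has 88.8% power at 260 patients and at least 93.1% at 300. The error is conservative only.
- A reader might infer that surgery type was deliberately excluded. Only centre's omission is stated.
- The documents give no clinic spread. Common transfusion triggers (3.1), the exclusion of fractures and serious bone grafting (3.3.3), and the expectation that revision rates are only a little higher (6.5) point to the milder end.
- No block size is given, and efficacy conclusions use the per-protocol set (6.3), where exclusions disturb balance. Perfect balance overstates the strata share.
- Strata may be sparse: 20 patients at a clinic × 30% revision / 2 arms = 3 per arm. Falling back to an exact stratified test can bring the conservatism back.

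None of this rescues the argument in 6.1.4, which the protocol settles itself rather than leaving to an analysis plan.

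**Conclusion.** The concern holds as an efficiency point. The reasoning in 6.1.4 is backwards, and the pooled Fisher test gives up power for two distinct reasons. Fisher's exactness costs about 2–3 points at 21% v 7% and about 5 at 21% v 10%. Ignoring the strata costs a further 0.3–1 point and about 1–3.5 points respectively with 300 patients; at 260 and strong spread the first figure reaches 1.7.

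The Fisher share at 21% v 7% follows from the protocol's own rates. The strata share rests on assumed clinic differences and perfect within-stratum balance, so it is an upper bound for each spread. The 21% v 10% effect is also assumed. No false positive claim becomes more likely, and no conclusion at the planned effect is endangered.

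**What to change.** In 6.1.4, 6.2 and 6.4, and in the synopsis to match, make the primary test a two-sided Cochran-Mantel-Haenszel test without continuity correction, stratified by the randomisation strata (clinic × primary/secondary surgery). Report the Mantel-Haenszel common risk difference with its 95% confidence interval. Keep pooled Fisher as a sensitivity analysis. Replace the sentence in 6.1.4 that uses balance as the reason to omit centre.

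Do not default to an exact or continuity-corrected stratified test. If strata prove very sparse, apply a pooling rule written in advance, such as stratifying by clinic only. Settle the wording before anyone sees outcomes by arm, including at the interim look in 6.6.

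The cost is wording, with the amendment steps in 7.4. Both factors are already in the Subject ID, and no extra patients are needed. One small downside: strata without any transfusion contribute nothing to the test.
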